#### Qualitative assessment analysis

All transcripts from the in-depth interviews and focus group discussions are transcribed in French if the activity was conducted in French and in English if the activity was conducted in the local language or English. For the analysis, an interim analysis process will be used. Major themes from the interviews and focus groups will be listed according to the objectives of the study before starting the analyses (a priori codes) and will be enriched if other themes will be found to be relevant to the study objectives (inductive codes). The analysis will be done using the software ATLAS.ti 8 2017.

#### Cost-effectiveness analysis

The two models of care will be analyzed and their cost-effectiveness in each country assessed.

The analysis will be from the healthcare system’s and the primary analysis will generate an incremental cost per Disability-Adjusted Life Year averted for the intervention model of care vs the standard of care, with a mathematical model used to extrapolate effects observed in the trial to a lifetime time horizon. Additional analyses will include reporting of patient costs incurred during illness and care-seeking, and an asset-based wealth quintile of participants, and generation of additional measures of health impact (deaths and TB cases averted).

### Ethical aspects

#### Protocol approval

The study protocol has been submitted and approved by two central Institutional Review Boards (IRBs): Advarra IRB from the USA, which is the sponsor’s institutional IRB, and WHO Ethics Research Committee. In addition, the protocol was submitted and approved by the local IRBs: Cameroon National Ethics Committee for Human Health Research and Research Ethics Committee of the Mbarara University of Science and Technology in Uganda. In Cameroon, it has also been approved by the Direction for Operational Research from the Ministry of Health and in Uganda by the Ugandan National Council for Science and Technology. Any change in the protocol or to the informed consent form that affects the scientific questions and study design or may affect a subject’s willingness to continue participation in the study were considered as amendment and are submitted to all previously described ethics committees after approval from the scientific committee and the sponsor.

#### Informed consent

All consent forms used for the CONTACT study have previously been approved by the central and local ethics committees. Written informed consent is obtained from index cases and contacts, who are informed of the study objectives, procedures, and their risks and benefits. In addition, children older than 7 years in Cameroon and 8 years in Uganda provide written informed assent. Participants with incapacity consent through their legal representative and illiterate participants consent through a witness who is not part of study staff. Country-specific informed consent forms are developed to allow for different standard of care specificities. For index cases, the TB focal person collects the informed consent at the inclusion visit. For contacts in the facility-based model, the TB focal person, assisted by the research assistant, collects the informed consent. In the community-based model, only the research assistant can collect the informed consent. Consent for HIV testing is included in the study consent form.

Individual consent is obtained by the researchers during qualitative activities: focus group discussions and in-depth interviews and also during the patient cost collection for the cost-effectiveness analysis.

#### Handling withdrawals

At any moment, a contact case can withdraw their consent without any consequence for their care and their data prior to the date of withdrawal are kept for analysis. Their case management continues under the NTP guidelines.

#### Confidentiality

Each participant has a unique study code. No directly identifying data is entered into the database. An identification log allows the research assistants to make the link between the code and the name if needed and this log is kept separately in locked study cabinets on site.

### Dissemination

The trial results will be published in peer-reviewed medical journals, preferably open access or guarantying an open access according to international guidelines for authorship. After approval by the scientific committee, the final trial report will be sent to the sponsor, Unitaid, the World Health Organization, and NTP officials.

## Discussion

The CONTACT study has several strengths and limitations.

### Strengths

Methodologically, the use of a randomized cluster-controlled design ensures a good level of evidence. The inter-cluster variability is taken into consideration by the use of a covariate-constrained randomization of the number of index cases per cluster. In addition, the study is using a comprehensive mixed-methods approach that looks at the study goal from different perspectives: quantitative, qualitative, and cost-effectiveness.

The intervention package was conceptualized in a very pragmatic and realistic manner after discussion with end-users, national TB program, and community representative to ensure that it could be implemented by the NTP at the end of the research period. In addition, the intervention is evaluated in two countries with similar TB burden, but very different health system organization and level of community engagement that increases the representativeness of the study results. In Cameroon, the national system is very centralized whereas in Uganda lower level health facilities are capacitated to do TB diagnosis and follow-up. In Uganda, over the last 2 decades, there have been several HIV-related interventions, many of which have been implemented in the communities. The population is used to community activities and a system of CHW is in place (called Village Health Teams) and articulated by the Ministry of Health. The package proposed by the CONTACT study has been inspired by the HIV and malaria community activities [42, 43] and integrates very well in the Ugandan context. Finally, all cluster facilities are supported by the CaP TB program for TB diagnosis and treatment, which reduces the risk of heterogeneity between the clusters and TB detection endpoint assessment bias.

The study is constructed on the framework already existent in the health facilities and uses the health personnel of these health facilities. The main strength is represented by their training and experience in working with TB, and the fact that they are already integrated in the national system, no study additional staff was hired for this purpose. The TB focal person and safety monitor receive an incentive for filling study-specific documentation that is outside their usual work.

### Limitations

Because the cluster sites were limited to the facilities supported by the CaP TB project, it was not possible to select more than 20 clusters. It was impossible to avoid urban facilities, which increases the inter-cluster variability and may increase the risk of cluster contamination due to the more complex system of patients’ reference in cities as compared to rural settings. The proportion of urban clusters is higher in Cameroon as the two selected regions where the CaP TB project takes place include the two biggest cities of the country. In Uganda, some clusters comprise two health facilities to allow for the necessary recruitment capacity and this operational limitation may introduce more heterogeneity in the measurement of the outcomes.

Another limitation is the reliability of source documents from facility registers as compared to study-specific source documents, which can induce an information bias and risk of missing data. To minimize this limitation, a register data quality check was done during the baseline period and in sites where inconsistencies were found, a training on data collection was recommended.

The training of facility personnel on the study procedures, the reinforcement of the study source documents, and the presence of research assistants is likely to increase the quality of the facility-based as compared to routine conditions and may have an effect on the expected difference of primary endpoint between the community-based and the facility-based models. Also, because the duration of the TPT is known to influence the completion of the TPT, which is part of the primary endpoint measure and because NTP was expected to change their guidelines in the coming months, we introduced the 3-month regimen in the facility-based model as well. Therefore, the study standard of care does not fully represent the current standard of care used in both countries. The choice of a very operational and pragmatic adherence measure likely to be well accepted by NTP (recording of the dose intake on a treatment card) relies on the parent/guardian’s understanding and reliability in recording the dose intake and could potentially introduce information bias or desirability bias. To prevent this risk, the CHW and research assistants are asked to systematically reconcile what is recorded by the parent/guardian on the treatment card with the pills remaining in the blisters. In the community-based model, two extra visits after 1 and 2 weeks after starting TPT were requested by the NTP to ensure that no child with TB disease was missed by the symptom screening done by CHW and to verify the tolerability. This results in more frequent assessments of treatment adherence and tolerability as compared to the monthly follow-up in the facility-based model and could introduce an observation bias that could affect the comparison of adherence and safety between the two models.

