Cascade of care for TB detection of adult contacts	Number of adults screened and proportion of adults screened among household identified adult contacts
	Proportion of adults with symptoms suggestive of TB: presumptive TB cases
	Proportion of adults presumptive TB cases diagnosed with TB
Safety and treatment adherence for children under TPT	Proportion of children with serious adverse events
	Proportion of children with adverse events of interest: peripheral neuropathy, clinical hepatotoxicity
	Ratio of dose taken as indicated (ticked) on the treatment card by the parent/guardian over the total number of doses to be taken by prescription
Endpoints at 6 months	Treatment outcomes of children started on TB treatment
	Proportion of children diagnosed with TB after initiation of TPT: during and after TPT
	Proportion of children diagnosed with TB among those who were not started on TPT and were not diagnosed with TB at baseline assessment
Before-after comparison for TB adult and pediatric cases and for TPT initiation and completion from health facility registers	Number of patients diagnosed with TB and registered
	Proportion of children among all patients diagnosed with TB and registered
	TB treatment outcomes of patients (adults and children) diagnosed with TB and registered
	Number of children started on TPT
	Completion rate of children started on TPT
Acceptability and feasibility of the intervention	Attitudes, willingness, and motivation to have a visit in their household
	Myths, anticipated fears, stigma, and risks of having a visit in their household
	Actual experiences with household visits
	Perception of the disease, its risk, and the notion of prevention, including TPT
	Description of critical events during house visits and how these were dealt with
	Identification of main constraints
Fidelity of the study	Proportion of delivered activities compared to the intended activities of the model
Cost-effectiveness of the intervention	Costs of CHW/community nurse assessment and treatment
	Costs of facility-based assessment and treatment
	Other facility costs (overheads, diagnosis, hospitalizations)
	Direct parent/guardian costs (related to care)
	Indirect parent/guardian costs (unrelated to care, e.g., dissaving, travel costs)

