### Description of the intervention

#### Facility-based model

This model implements a “passive” approach to the screening and management of household contacts (see definition in the “Study population” section) at the facility level as per current practice. Implementation follows current National Tuberculosis Program (NTP) recommendations, except that a 3-month regimen of daily rifampicin-isoniazid (3RH) as a fixed-dose combination (FDC) is offered as TPT to eligible child contacts. In the context of the study, sites also benefit from additional data collection and trainings with follow-up support for the facility staff.

When a person is diagnosed with bacteriologically confirmed pulmonary TB (index case), the facility staff in charge of TB (TB focal person) asks the index case to bring all household contacts with TB-related symptoms, all young (< 5 years) child contacts or older (5–14 years) child contacts living with HIV or exposed to HIV, irrespective of symptoms, to the health facility for evaluation for TB disease or for eligibility for TPT. This facility-based model is currently implemented in district hospitals in Cameroon for child contacts under 5 years old, but poorly applied for child contacts 5–14 living with HIV. In Uganda, the NTP allows household contact tracing when feasible but evaluation, TPT initiation, and follow-up are required to be done at the facility. In practice, due to lack of transport, the household contact tracing was poorly implemented. In both countries, at facility, TB investigations include clinical examination, sample collection for smear microscopy or Xpert MTB/RIF testing, and CXR when available and indicated, i.e., Xpert is negative or not done. Any contact diagnosed with TB is commenced on TB treatment, registered, and provided with treatment support and follow-up as per NTP guidelines. All sites are supported by the CaP TB program reducing the risk of heterogeneity of diagnosis and treatment of pediatric TB between sites and the two countries. Asymptomatic children who are eligible to receive TPT as 3RH (or 6H if drug-drug interactions with antiretroviral therapy preclude the use of rifampicin) are initiated at the facility with monthly follow-up (Fig. 1). The schedule of the facility-based model is presented in Table 2.

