**Interventions**											
**Facility-based arm**			X	X			X	X	X	X	
**Community-based arm**			X	X	X	X	X	X	X	X	
**Qualitative assessment**		X									X
**CEA**					X						

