**Assessments**											
**Identification of contact children**			X								
**Children started on TPT**				X							
**Children completed TPT**									X	X	
**Acceptability of the intervention**		X									X
**TPT cost**					X						

*Abbreviations*: *W* week, *CEA* cost-effectiveness analysis, *TPT* TB preventive therapy

*Allocation takes place before the intervention begins as the clusters are randomized and not the individuals

**The baseline phase takes place 3 months before the intervention phase

***Children started on 6 months of isoniazid have 2 additional follow-up visits at week 16 and week 20

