#### Community-based model

The intervention model is a decentralized, “active” approach to the screening and management of household contacts and is community-based. When an index case is diagnosed with bacteriologically confirmed pulmonary TB, the TB focal person asks whether s/he has child contacts in the household, and if so, then asks whether s/he is willing to receive a team in his/her household for contact symptom screening. If they agree, then an appointment is made and a team comprising a trained community health worker (CHW) and a research assistant goes in the household to screen all contacts (children and adults). If the index case does not have contact children in their household, then s/he is not included in the study, but contact investigation is done under routine care by the TB focal person. During the contact screening visit, the contacts who present symptoms of TB are referred to the health facility for TB investigations. Those who are asymptomatic and eligible for TPT (i.e., < 5 years irrespective of HIV status or 5–14 years and living with HIV) receive another visit by the TB focal person or TB nurse to initiate 3RH (or 6H if drug-drug interactions with antiretroviral therapy preclude the use of rifampicin). The follow-up is done at the household by the CHW after 1 week, 2 weeks, and then monthly in order to rapidly identify the children who develop TB symptoms in the community. The CHW collects the TPT at the health facility before each household visit and brings the remaining pills and documents back to the facility after the visit. During the follow-up visits, the CHW repeats the TB symptom screening, assesses the child’s TPT tolerability and adherence, and assesses the presence of any critical sign. If the child presents critical danger signs, tolerability problems, or TB symptoms, s/he is immediately referred to the health facility for a clinician to consult them (Fig. 2). The schedule of the community-based model is presented in Table 2.

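### Tolerability is checked five times by week 12 in the community arm and three times in the facility arm; the article names the resulting bias but states no analysis to gauge it for non-serious safety findings

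*Protocol article*

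**What the plan says.** For the community arm, the Community-based model section states: "The follow-up is done at the household by the CHW after 1 week, 2 weeks, and then monthly". For the facility arm, the Facility-based model section says that eligible children "are initiated at the facility with monthly follow-up". Table 2 agrees: the row "Community-based arm" is marked at weeks 1, 2, 4, 8, 12 and 24, and the row "Facility-based arm" at weeks 4, 8, 12 and 24. A footnote to the table adds: "Children started on 6 months of isoniazid have 2 additional follow-up visits at week 16 and week 20". It makes no distinction by arm.

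The Safety assessment section has tolerability checked against a standard list of signs at every follow-up visit. Secondary objective (iii) compares the two models on tolerability and adherence. The matching safety endpoints in Table 1 are the proportion with serious adverse events and "Proportion of children with adverse events of interest: peripheral neuropathy, clinical hepatotoxicity". Neither is limited to particular visits.

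The Limitations section explains that "two extra visits after 1 and 2 weeks after starting TPT were requested by the NTP" and concedes that the more frequent assessment "could introduce an observation bias that could affect the comparison of adherence and safety between the two models".

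**The concern.** If signs are sought by checklist at each visit, the number of children with a recorded event depends partly on how often they are asked. The arm with more visits can then show more events even when the drug is tolerated equally well in both. Random allocation of clusters does not protect against this, because the difference in looking is built into the arms. A mixed model with a cluster effect does not remove it either.

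The article usually follows an anticipated bias with a remedy. Doubtful treatment cards are reconciled with blister packs, weak registers get a quality check and training, and disagreement over the number of declared children gets a named sensitivity analysis. The unequal visit schedule is admitted and left there. At stake is the reading of a secondary safety result: a higher proportion of events under the community model could not be separated from more frequent questioning, and that model is meant for later scale-up.

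**Working it through.** **1. Visit count (Table 2, up to week 12)**

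- Community: weeks 1, 2, 4, 8, 12 = 5 checks.
- Facility: weeks 4, 8, 12 = 3 checks.
- Difference: 5 − 3 = 2, at weeks 1 and 2. This reproduces the two extra visits given in the Limitations section. Ratio: 5 / 3 = 1.67.
- Week 24 is marked for both arms, and weeks 16 and 20 apply to children on the 6-month regimen in either arm. Neither changes the difference.

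**2. What the unequal count could do**

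The documents give no rate or duration for any adverse event, so the following is an illustration under stated assumptions: equal true risk in both arms, onset spread evenly over 84 days, a sign recorded only if present on the day of a visit, and no recall of signs that have gone.

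A sign lasting L days is seen at a visit on day v if it began in the L days before v. The share detected is the number of days covered by at least one such window, divided by 84. Visits fall on days 7, 14, 28, 56 and 84 (community) and days 28, 56 and 84 (facility).

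| Duration L | Community | Facility | Ratio |
|---|---|---|---|
| 3 days | 5 × 3 / 84 = 17.9% | 3 × 3 / 84 = 10.7% | 1.67 |
| 7 days | 5 × 7 / 84 = 41.7% | 3 × 7 / 84 = 25.0% | 1.67 |
| 14 days | 56 / 84 = 66.7% | 3 × 14 / 84 = 50.0% | 1.33 |
| 28 days | 84 / 84 = 100% | 84 / 84 = 100% | 1.00 |

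At 14 days the windows before days 7 and 14 overlap: together they cover days 0 to 14 only, so the community total is 14 + 14 + 14 + 14 = 56 days.

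**3. How the assumptions move this**

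Recall of early complaints at the week 4 visit would pull the ratio towards 1. Onset concentrated in the first two weeks would push it up: a 7-day sign that starts by day 14 is gone by day 21, before the first facility visit on day 28. The range 1.0 to 1.67 is therefore a guide, not a bound.

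**4. After restriction to shared visits**

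By week 12 there are 3 checks against 3, and with week 24 there are 4 against 4.

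**The case against.** The strongest reply is that the authors disclose the bias themselves, that a journal article condenses the full protocol, and that a shared-visit analysis may already sit in a statistical analysis plan that is not shown. That limits the weight of the point. It does not remove it, because the article names this specific bias and a planned comparison that it affects, and states nothing to address it.

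Several further objections stand and set the limits of the point:

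- A reader might infer that the plan compares every recorded complaint. It does not say so. Table 1 lists serious adverse events and two named events of interest, and has no endpoint for any event. A checklist complaint goes to a clinician for examination before it becomes a diagnosis. The sentence on the mixed model for secondary outcomes names only the care-cascade endpoints, so the article does not fix a model for safety.
- A reader might put a definite size on the bias. A 5% chance of a complaint at each visit, independent between visits, gives 1 − 0.95³ = 14.3% against 1 − 0.95⁵ = 22.6%, an excess of about 8 points. The 5% has no source in the documents, independence means that no complaint persists from one visit to the next, and the quantity is not a Table 1 endpoint.
- A reader might extend the remedy to adherence. The endpoint there is doses ticked over doses prescribed, which is cumulative. Card readings at weeks 4, 8 and 12 already include the first two weeks, so a visit restriction would barely change it. Any gain in adherence from the early visits belongs to the intervention effect.
- A shared-visit comparison used alone could err the other way. An early sign found at week 1 or 2 in the community arm is referred at once and may be gone by week 4, while the same sign persisting in the facility arm would be counted.

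**Conclusion.** The point holds for the secondary comparison of adverse events of interest and other non-serious tolerability findings, and only there. The schedule of five checks against three and the admitted bias are facts of the document; the size is not. Under even onset and no recall, the ratio of detected events could run from about 1.0 for signs lasting 28 days or more, through 1.33 at 14 days, to about 1.67 at 7 days or less.

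The documents do not support reading this as a flaw in the primary endpoint, which is initiation and completion of preventive therapy, or as a reason to discard the week 1 and 2 findings. Serious adverse events depend less on visit frequency and need no restriction. This is a cheap improvement to secondary safety reporting, not a defect that threatens the trial's main conclusion.

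**What to change.** Keep the full count of adverse events of interest and other non-serious tolerability findings in both arms. Before the analysis, specify beside it:

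- a sensitivity comparison restricted to findings from visits shared by both arms: weeks 4, 8, 12 and 24, and also weeks 16 and 20 for children on the 6-month regimen;
- a separate report of events first found at weeks 1 and 2 in the community arm.

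Count serious adverse events in full in both arms, and leave the dose-ratio adherence endpoint as defined. If the statistical analysis plan already contains such an analysis, a sentence pointing to it is enough.

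The cost is a filter by visit and one extra table, using data already collected; no visit or study procedure changes. The drawback is that the shared-visit result may understate community-arm events that were found early and had resolved by week 4. The two results should therefore be presented and read together.
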